### Data management {19}

Data collection is pseudonymised using a four-digit personal code, which is assigned to each participant in addition to their MiA code. The identification list is stored securely in a password-protected file.

Questionnaires are manually entered into IBM SPSS Statistics, version 29 (IBM Corp., Armonk, NY) [69], using a standardised codebook. Data entry is performed according to the double-entry principle. The two resulting datasets are systematically compared independently by a member of the data management team to identify and correct discrepancies. All differences are documented in order to assess the error rate. Signed consent forms are archived securely and separately from the questionnaires in locked cabinets.

### Confidentiality {27}

App access creation and data management are conducted via the web-based dashboard in which no personal data of the participants is stored. Personal identification is only possible via the separate allocation list. Data entered in the app (e.g. behaviour tracking and photos) are transmitted in encrypted form and stored on servers in Germany for 10 years. The user’s IP address changes with each login and is not stored in the app or in the dashboard. The International Mobile Equipment Identity (IMEI) is not used or stored in the app or in the dashboard.

All questionnaires are completed using paper forms. Data entry and statistical analysis are conducted by members of the in-house research team. Data will not be passed on to external parties.

The assignment list and study data are stored separately in password-protected folders. Consent forms are archived separately from the questionnaires. All data will be deleted no earlier than 10 years after study completion. Paper questionnaires will be destroyed promptly after completion of the study.

### Plans for collection, laboratory evaluation, and storage of biological specimens for genetic or molecular analysis in this trial/future use {33}

This trial will not involve the collection, laboratory evaluation, or storage of biological specimens for genetic or molecular analysis.

## Statistical methods

### Statistical methods for primary and secondary outcomes {20a}

Statistical analysis will be performed using IBM SPSS Statistics, version 29 (IBM Corp., Armonk, NY [69]). Descriptive statistical analyses will be performed to summarise patient characteristics, patient-reported outcome measures (e.g. individually assessed health, excluding the clinically assessed OHSI) and to compare groups. In the intervention arm, app usage metrics (e.g. duration and engagement) will be summarised descriptively. These analyses will include measures of central tendency (mean, median) and dispersion (range, variance, standard deviation).

For the analysis of the primary and secondary outcomes, a linear mixed model (LMM) will be used as the preferred statistical method. LMMs account for intra-group correlations (e.g. within the intervention and control groups) due to repeated measurements at time points t1–t4.

The study is designed as an efficacy trial to evaluate whether the app improves skin protection behaviour (primary outcome). Given that the app is intended as a self-management tool, the analysis will also explore its potential to support patients in independently maintaining skin health over the longer term. The LMMs will model change scores, with a pre-specific focus on the contrast between baseline (t1) and follow-up (t4). The intervention contrast will test whether the change in skin protection behaviour is significantly greater in the intervention group than in the control group. This contrast constitutes the statistical test of the intervention effect, operationalised as a group-by-time interaction.

A key advantage of LMMs is their robustness to missing data, which are common in longitudinal studies. Furthermore, LMMs allow the estimation of covariance structures even in studies with relatively small sample sizes, thereby improving the reliability of the results. All analyses will be conducted according to the intention-to-treat (ITT) principle, meaning that all randomised participants will be analysed in the groups to which they were originally assigned, regardless of their level of adherence to the intervention. This approach ensures that the effect estimates reflect the effectiveness of the intervention under real-world conditions. We acknowledge that variation in app usage in the intervention arm may attenuate the observed ITT effect; therefore, app usage will be summarised descriptively, and a pre-specified per-protocol sensitivity analysis will be conducted to assess robustness. To assess the robustness of the results, additional sensitivity analyses will be conducted, including a per-protocol (PP) analysis, which will consider only those participants who adhered to the study protocol as specified. This will include participants who complete all required assessments and, in the intervention group, use the app as specified. Comparing the results of ITT and PP analyses will enable for a more comprehensive evaluation of the stability and reliability of the findings. The significance level is set at *p* = 0.05. An overview of the intended analysis strategies is presented in Table 2.

**Table 2 Tab2:** Overview of planned statistical methods

Category	Outcome	Statistical analyses methods
Primary	Skin protection behaviour	• Statistical model: linear mixed model (LMM) (change t1 to t4)
Secondary	Skin condition of the hands (self-assessed; school grades: ordinal)	• Descriptive: mean value per group and time point • Statistical model: generalised linear mixed model (GLMM)
Secondary	Action control	• Descriptive statistics: mean and standard deviation per group and measurement time • Statistical model: LMM
Secondary	Health-related quality of life	• Statistical model: LMM
Secondary	Employment status	• Descriptive; two-sample *t*-test
Secondary	Sick days due to skin condition	• Descriptive; two-sample *t*-test
Further (intervention group only)	MiA app impact on goal achievement	• Descriptive
Further (intervention group only)	MiA usage (daily values (182) per person)	• Descriptive ○ Daily usage frequency (mean, median, range, standard deviation) ○ Usage distribution by user group (frequencies, percentages) ○ Usage trends over time (time series plots, moving averages) • Correlation coefficient between measurement points ○ To analyse usage, mean scores are planned to be calculated over the intervals between t2 and t3, t2 and t4, and t3 and t4

Abbreviations: *GLMM *generalised linear mixed model, *LMM *linear mixed model

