### Trial design {8}

The study ‘TecNaP-RCT’ is designed as a non-blinded quasi-randomised, controlled superiority trial with two parallel groups (intervention and control groups). Patients will be assigned to intervention and control groups in clusters based on their admission dates.

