### Sample size {14}

The anticipated primary outcome of the study is the improved skin protection behaviour of participants. The following assumptions and calculations form the basis for determining the total sample size: the sample size was planned a priori based on a *t*-test for independent samples, comparing the change scores (difference between t1 and t4) between the intervention and control groups. A mean effect size of *d* = 0.4 was assumed to determine the required sample size. This anticipated effect is expected to lie in the lower range between small and medium. With a significance level of *α* = 0.05 (two-tailed), a statistical power of 1 − *β* = 0.80, and an expected dropout rate of 30%, the required total sample size was calculated to be *N* = 286 participants. This total sample will be divided into the following groups: intervention group with *n* = 143 participants and control group with *n* = 143 participants. The dropout rate of 30% was based on literature reporting the effectiveness of app-based interventions for behaviour change [66, 67]. Previous studies have also indicated that the actual response rate in app-based interventions may, in some cases, exceed the projected dropout rate of 30%. The sample size calculation was conducted using G*Power software version 3.1.9.7 [68].

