## Assignment of interventions: allocation

### Sequence generation {16a}

Participants will be allocated to either the intervention or control group in clusters based on their admission date at the clinic, following a predetermined quasi-randomisation allocation scheme. The assignment to the intervention or control group is thus planned prior to the start of the study. This pragmatic approach is justified for several reasons: firstly, patients will participate in a 3-week inpatient maintenance programme. Given the duration of their stay and the potential for interpersonal interactions, it is essential to incorporate designated wash-out periods to prevent contamination between groups. Additionally, participants will be allocated in clusters rather than at the individual level. Therefore, to ensure the study is completed within an appropriate timeframe, no alternative method of random group allocation is feasible. Furthermore, to minimise potential confounding due to seasonal factors and occupational patterns, the allocation scheme ensures that participants in both groups are recruited continuously throughout the entire year. This is important because climatic influences (such as winter cold) and the seasonal admission of certain occupational groups (e.g. construction workers more often admitted in winter) may affect outcomes; thus, both groups are exposed to these factors equally.

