#### Quasi-randomisation

In this trial, allocation to the intervention and control groups is conducted in clusters based on the date of admission to the clinic. This constitutes a pragmatic, quasi-randomised approach rather than strict randomisation and, as such, carries a risk of bias. In particular, confounding may influence any observed effects (i.e. differences in outcomes could be attributable to factors other than the intervention) [86]. Moreover, quasi-randomisation and the absence of allocation concealment render the study susceptible to allocation and selection bias. Knowledge of forthcoming group assignment may lead to systematic differences between groups and, in turn, affect study outcomes [86, 89]. Accordingly, we plan adjustment analyses (e.g. in the event of baseline imbalances) and will conduct sensitivity analyses to test the robustness of the results.

Notwithstanding these limitations, the chosen allocation method is a pragmatic alternative that enables the generation of decision-relevant evidence for the care of patients with WRHE. Quasi-experimental designs are well suited to producing causal inferences that are applicable to real-world implementation [90]. This is particularly pertinent here, as the TIP inpatient rehabilitation programme operates within relatively fixed parameters (treatment, patient education and counselling workflows) that align more naturally with a pragmatic study design than with an artificial experimental setting—an approach that could otherwise threaten external validity. In addition to the planned adjustment and sensitivity analyses, we will report the study in accordance with the updated guideline for reporting randomised trials (CONSORT 2025 Statement [91]) with particular attention to the CONSORT extension for cluster trials [92].

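### Patients are allocated in admission-date clusters, but neither the stated model, the two t-tests nor the sample size allows for clustering of the change from t1 to t4

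*Protocol article*

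**What the plan says.** **Allocation.** Under Trial design {8}: "Patients will be assigned to intervention and control groups in clusters based on their admission dates". Sequence generation {16a} repeats it: "Additionally, participants will be allocated in clusters rather than at the individual level". Recruitment {15} describes an intervention-only phase, a 3-week wash-out and a control-only phase, after which the cycle repeats. The window runs from 13 May 2025 to about 2 October 2026. The number and length of the phases are not given.

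**Analysis.** Statistical methods {20a} says of the mixed models: "LMMs account for intra-group correlations (e.g. within the intervention and control groups) due to repeated measurements at time points t1–t4". The primary test is the t1-to-t4 difference between arms: "This contrast constitutes the statistical test of the intervention effect, operationalised as a group-by-time interaction". The Table 2 entry for the primary outcome reads "Statistical model: linear mixed model (LMM) (change t1 to t4", with no cluster term. Table 2 assigns two-sample t-tests to employment status and sick days. The section on missing data {20c} is silent on clustering.

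**Sample size {14}.** "the sample size was planned a priori based on a *t*-test for independent samples", comparing change scores. The assumed effect is d = 0.4, with 80% power, two-sided 5% and 30% dropout.

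**Other mention of clusters.** The Quasi-randomisation limitation promises adjustment, for example for baseline imbalance, unspecified sensitivity analyses, and reporting "with particular attention to the CONSORT extension for cluster trials". That is a reporting commitment and does not specify an analysis.

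**The concern.** When groups of patients are allocated together, the precision of the treatment comparison depends on how much the analysed quantity varies between those groups. A model that knows only about repeated measurements within a patient treats the roughly 200 patients expected at t4 as 200 independent pieces of evidence. If it varies between clusters, the standard error is then too small, the interval too narrow and the 5% test rejects too often. With few clusters the degrees of freedom are overstated as well.

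The article itself names reasons why the change could be shared within a cluster. Group education and supervised training take place during the inpatient stay, after enrolment on the admission day. Patients mix during that stay, which is why wash-outs were introduced. Season is said to affect outcomes, and because t4 falls six months after discharge, patients admitted together pass through the same seasons between t1 and t4. All of this makes a positive ICC of the change plausible. None of it gives a value.

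**Working it through.** **1. The plan's own figure.** Inputs from Sample size {14}: d = 0.4, two-sided alpha 0.05, power 0.80, dropout 30%, 1:1. The noncentral t calculation gives 100 per arm (power 0.804). Then 100/0.7 = 142.9, so 143 per arm and 286 in total. This matches the article exactly and leaves no room for a design effect.

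**2. Which clustering matters.** Write a patient's score as cluster level c plus own value y. If c is the same at both times, the change is (c + y4) − (c + y1) = y4 − y1, and c disappears. In simulation with a stable shift only, the type I error was 0.049. Only a cluster effect on the change itself inflates the primary test, so every ICC below is an ICC of the change score.

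**3. Inflation.** Assumptions, none of them in the article: 200 analysed patients, equal cluster size m, ICC 0.01 to 0.05.

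- Design effect: DE = 1 + (m − 1) × ICC.
- Standard error understated by a factor of √DE.
- Actual type I error of a test that ignores clusters: 2 × [1 − Φ(1.96/√DE)].

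Example: 4 clusters, m = 50, ICC 0.05. DE = 1 + 49 × 0.05 = 3.45; √3.45 = 1.86; 1.96/1.86 ≈ 1.055; type I error ≈ 0.29.

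| Clusters (m) | DE, ICC 0.01 / 0.02 / 0.05 | Type I error, same ICCs |
|---|---|---|
| 50 (4), weekly cohorts | 1.03 / 1.06 / 1.15 | 5.4% / 5.7% / 6.8% |
| 20 (10) | 1.09 / 1.18 / 1.45 | 6.0% / 7.1% / 10.4% |
| 10 (20) | 1.19 / 1.38 / 1.95 | 7.2% / 9.5% / 16.0% |
| 8 (25) | 1.24 / 1.48 / 2.20 | 7.8% / 10.7% / 18.6% |
| 4 (50) | 1.49 / 1.98 / 3.45 | 10.8% / 16.4% / 29.1% |

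Simulated t-tests on change scores (4,000 null trials per setting) agree: 11%, 17% and 28% for 4 clusters, 8%, 11% and 20% for 8, and 6%, 7% and 11% for 20. A t-test on cluster means kept its 5% level in the settings simulated (weekly cohorts of about 4, 10 phases and 4 phases).

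**4. What the recruitment window allows.** It spans 507 days, or 72.4 weeks. Suppose phases last at least one week and a wash-out follows each intervention phase. One cycle then takes 1 + 3 + 1 = 5 weeks, so about 14.5 cycles, or 29 phases, fit at most. That is 200/29 ≈ 6.9 patients per phase, with DE 1.06 to 1.30 and type I error 5.7% to 8.5%. If the phase is the cluster, the weekly-cohort row is therefore too mild.

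**5. Power when clustering is respected.** The noncentrality is 0.4 × √(100/(2 × DE)), on (clusters − 2) degrees of freedom, for ICC 0.01 to 0.05:

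- 20 clusters: 0.73 to 0.60
- 10 clusters: 0.62 to 0.43
- 8 clusters: 0.57 to 0.36
- 4 clusters: 0.27 to 0.15

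**The case against.** The strongest reply is that the sentence on mixed models describes what such models do in general and does not list the trial's random effects. The article names none, not even one for the patient. It condenses a fuller plan, random-effects structure is usually left to the analysis plan, and the commitment to cluster-trial reporting shows that the authors know their design. This stands in part: the article names no cluster term, but it cannot be said to exclude one. It does not dispose of the point. The one correlation source it names is repeated measurement; the reference to correlation within the two arms does not help, because an arm is not an admission cluster. The two t-tests and the printed sample size also assume independent patients, and an unseen plan could not add clustering without departing from them.

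Three stronger readings are tempting, and the document does not support them:

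- **Any positive ICC biases the primary test.** It does not. An ICC in level alone cancels; only an ICC of the change counts. Occupational mix, for instance, may act largely on level.
- **The cluster is the recruitment phase.** The article says only that clusters are based on admission date. Its statement that both groups are recruited throughout the year favours more, shorter phases.
- **The type I error is near 30%.** That needs only four phases and an ICC of 0.05. Recruitment {15} describes at least four phases and gives no total.

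**Conclusion.** The concern holds in conditional form. The unit of allocation is a cluster, while the stated correlation source, the two t-tests and the sample size treat patients as independent apart from repeated measures. If the t1-to-t4 change is correlated within clusters, which is plausible but not shown, the primary p-value and interval are too optimistic. The same applies to the other mixed-model contrasts. Sick days are counted over follow-up and are not a change score, so nothing cancels there.

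The size cannot be settled from the article. Across change-score ICCs of 0.01 to 0.05 it runs from near nominal (5.4% to 6.8% with weekly cohorts of four) through 7% to 16% (10 phases) to 11% to 29% (4 phases). A reader might infer that the primary result will certainly be anti-conservative, or badly so; the document supports neither. It does support the conclusion that validity depends on an independence the design does not provide, and that this should be put right before the data are analysed.

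**What to change.** 1. Define the cluster: recruitment phase, admission cohort, or cohort within phase. State how many there are.
2. In each LMM and GLMM that keeps t1 in the outcome vector, add a cluster-by-time random effect; a cluster intercept alone cancels out of the contrast. If the change score is the outcome, add a cluster random effect. For the LMMs use Satterthwaite or Kenward-Roger degrees of freedom, and state a comparable small-sample approach for the GLMM.
3. Replace the two t-tests in Table 2 with cluster-adjusted analyses.
4. Add an analysis of cluster means as a check. Use a permutation test only if there are enough phases. With 2 versus 2 phases there are 6 arrangements and the smallest two-sided p is 2/6 = 0.33; with 3 versus 3 it is 2/20 = 0.10. Because the phases alternate on a fixed scheme, free permutation also lacks a randomisation basis.
5. Restate power for assumed change-score ICCs and the actual cluster count.

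**Cost.** The wording and syntax are minor: admission date determines allocation, so the cluster identifier already exists. Recruitment is expected to run to October 2026 and no interim analysis is planned, so the change can be made before results are seen. The real cost is wider intervals and power below the stated 80%, for example 0.57 to 0.36 with 8 clusters. With only four clusters the cluster-mean test has 2 degrees of freedom (critical value 4.30) and little power. The sponsor should say so openly.

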### Outcomes {12}

The desired primary outcome of this study is a change in the participants’ skin protection behaviour, which encompasses the implementation of skin protection measures, cleansing, and care routines in both occupational settings and private daily life. Skin protection behaviour will be measured using a 13-item instrument adapted from the scale used by Matterne et al. [59] and expanded to reflect the content of the skin protection seminars delivered within TIP. The 13 items will be aggregated into a single total score. Items are rated on a 5-point Likert scale; the total score is the mean of all items (higher values indicate better skin protection), with item 11 reverse-coded. The specific items are presented in the Supplementary information (see Additional files 1–3). The primary analysis will compare the change in the mean primary outcome score for each participant from baseline to t4 (6 months after discharge from the clinic) between groups.

The anticipated primary outcome of this study is critical, as adequate skin protection behaviour can have a significant impact on disease course and thus contribute to both the stabilisation of the skin condition and improved disease management in occupational and private settings. Furthermore, it is a commonly used outcome to evaluate the effect of patient education in trials involving patients with WRHE [37, 40, 60].

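### The primary mixed model is described in two ways that do not fit together, and adjustment for the baseline score is not fixed in advance

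*Protocol article*

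**What the plan says.** The endpoint is clear. Outcomes {12} states: "The primary analysis will compare the change in the mean primary outcome score for each participant from baseline to t4", compared between groups. Sample size {14} plans a t-test "comparing the change scores (difference between t1 and t4) between the intervention and control groups", and Table 2 lists a linear mixed model for the change from t1 to t4.

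The model is less clear. Statistical methods {20a} first describes mixed models for repeated measurements at t1 to t4. It then says: "The LMMs will model change scores, with a pre-specific focus on the contrast between baseline (t1) and follow-up (t4". After stating that the contrast asks whether change is greater in the intervention group, it adds: "This contrast constitutes the statistical test of the intervention effect, operationalised as a group-by-time interaction".

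No baseline covariate is named for the primary model. The limitations section on quasi-randomisation plans adjustment analyses, with baseline imbalance as the example of when they would be used. It does not say which covariates would enter or whether the adjusted result would replace the primary one.

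**The concern.** Modelling change scores and testing a group-by-time interaction belong to two different models. Once t1 has been subtracted, it is no longer a response. The effect at t4 is then the group difference in change at t4, and the interaction asks something else: whether that difference varies across t2, t3 and t4. Two analysts could follow the same paragraph and report different primary p-values.

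The second part does not depend on the reading. The t1 score is collected but is not used as a covariate, so precision is given up. Adjustment that is triggered by observed imbalance also makes the primary estimate depend on the data. That matters more here than usual, because allocation is unconcealed and the article says the analyst also recruits participants and conducts goal-setting interviews.

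**Working it through.** **Inputs from Sample size {14}.** d = 0.4 in SD units of the t1-to-t4 change, two-sided α = 0.05, power 0.80, dropout 30%, 1:1 allocation. The t1–t4 correlation ρ is not given, so values are assumed below.

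**The plan's own figure.** A two-sample t-test (noncentral t) with d = 0.4 needs 100 per arm, with power 0.804. Then 200 / (1 − 0.30) = 285.7, so 286. The stated total reproduces.

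**What each reading tests.** Let Δ2, Δ3 and Δ4 be the true group differences in change from t1 at each later visit.

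- *Raw scores at t1 to t4.* The t4-versus-t1 interaction contrast is Δ4, which is the endpoint. In simulation (4,000 runs, 100 per arm, equal correlations of 0.5, so the SD of change is √(2 × 0.5) = 1) it estimated 0.40 with power 0.80.
- *Changes from t1 at t2, t3 and t4.* The t4-versus-t2 interaction contrast is Δ4 − Δ2. Results in the same simulation:

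| Δ2 / Δ3 / Δ4 | Mean estimate | Rejection rate |
|---|---|---|
| 0.4 / 0.4 / 0.4 | 0.00 | 5% |
| 0.2 / 0.4 / 0.4 | 0.20 | 29% |
| 0 / 0.4 / 0.4 | 0.40 | 80% |

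- *The t1-to-t4 change as the only outcome.* There is no time factor, so there is no interaction to test.

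The literal change-score reading therefore loses power only to the extent that an effect already exists at t2.

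**Value of the baseline score.** With equal variance σ² at t1 and t4:

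- variance of the change = 2σ²(1 − ρ)
- residual variance given t1 = σ²(1 − ρ²)
- ratio = (1 − ρ²) / (2(1 − ρ)) = (1 + ρ)/2

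The same raw effect then corresponds to d = 0.4 / √((1 + ρ)/2). With 100 completers per arm:

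| Assumed ρ | Variance ratio | Effective d | Power |
|---|---|---|---|
| change score | 1 | 0.400 | 80% |
| 0.3 | 0.65 | 0.496 | 94% |
| 0.5 | 0.75 | 0.462 | 90% |
| 0.7 | 0.85 | 0.434 | 86% |

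A simulated baseline-adjusted analysis at t4 with ρ = 0.5 also gave 90%. All these figures ignore clustering by admission date.

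**The case against.** A reader might infer that the primary test targets the wrong effect and would miss a sustained benefit. The article does not support that. The same paragraph names repeated measurements at t1 to t4, singles out the t1-to-t4 contrast and says in words that it compares change between groups. Taken together, this points to raw scores and the correct contrast. The change-score reading keeps one phrase and sets the others aside, and no t4-versus-t2 comparison is named anywhere.

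The low rejection rates also need an effect at t2. According to the limitations section, t2 lies before discharge, while the maintenance programme begins on the day of discharge. By t2 the intervention arm has had one interview on day 16 or 17 and an app test phase. Some effect by then is possible, but the full 6-month effect is unlikely. Table 1 is not shown, so measurement of the primary outcome at t2 and t3 is itself inferred from the methods text. All of this stands.

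It is also fair that a difference-in-change analysis is recognised and valid, that the trial was sized for it, and that a mixed model uses incomplete records which a t-test would drop. Leaving out a covariate costs efficiency, not validity. A separate analysis plan may settle the parameterisation. What remains is that the published text contains an internal contradiction about its only primary test and makes baseline adjustment conditional. The planned review by an independent statistician comes after study completion, so it cannot fix that choice in advance.

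A reader might also infer that calendar-based allocation makes the adjusted and unadjusted estimates target the same quantity. That is too strong. The article reports seasonal admission of occupational groups, says patients learn their arm before consenting, and concedes a risk of selection bias. If baselines differ, the two estimates can differ.

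**Conclusion.** The concern holds as a contradictory specification and an unused, conditionally adjusted baseline. It does not establish a wrong estimand or a fault in the sample size: under the raw-score reading the planned test is the stated endpoint with its planned power. The loss under the literal change-score reading is conditional on an effect at t2 and should not be quoted as the expected performance of the trial.

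The part that survives every reading is precision. Adjusting for t1 multiplies the variance by (1 + ρ)/2, which is worth roughly 6 to 14 percentage points of nominal power for ρ between 0.7 and 0.3. This assumes equal variances at t1 and t4, 100 completers per arm and no clustering; the correlations are assumptions. Fixing the adjustment beforehand also removes a data-dependent choice from an unblinded analyst.

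**What to change.** State one primary model before the data are analysed:

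- outcome: the raw skin protection score at each post-baseline visit
- fixed effects: group, time, group × time, t1 score and t1 score × time
- primary test: the single-degree-of-freedom group difference at t4

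Remove the statement that the model's outcome is a change score, and make the t1 adjustment unconditional. Report the unadjusted difference in change from t1 to t4 as a named sensitivity analysis, because allocation is quasi-random and unconcealed and the two estimates may diverge.

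No new data are needed: t1 is already collected and recruitment is expected to run until October 2026. The change is confined to the text of the plan, but it can alter the primary estimate if baselines differ. It should therefore be recorded as an amendment with its date and reason.

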### Methods in analysis to handle protocol non-adherence and any statistical methods to handle missing data {20c}

The primary analysis will be performed using linear mixed models (LMM), which provide valid estimates under the assumption of missing at random (MAR). To address protocol non-adherence, the analysis will follow the intention-to-treat (ITT) principle, including all randomised participants according to their assigned groups. Additionally, sensitivity analyses will be conducted, including per-protocol (PP) analyses, to assess the impact of protocol adherence on the study outcomes.

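### The plan says every analysis includes all randomised participants, but the t-tests named for employment status and sick days cannot include those without a follow-up value (minor; two secondary outcomes)

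*Protocol article*

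**What the plan says.** Section {20a} of the protocol article sets one rule for every analysis: "All analyses will be conducted according to the intention-to-treat (ITT) principle, meaning that all randomised participants will be analysed", and the sentence goes on "in the groups to which they were originally assigned, regardless of their level of adherence to the intervention". Section {20c}, which covers non-adherence and missing data, repeats the rule: "including all randomised participants according to their assigned groups".

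On method, {20a} says: "For the analysis of the primary and secondary outcomes, a linear mixed model (LMM) will be used as the preferred statistical method". It presents tolerance of missing data as a main advantage of such models. Section {20c} is narrower: "The primary analysis will be performed using linear mixed models (LMM), which provide valid estimates under the assumption of missing at random (MAR"). It names no imputation and no other missing-data method.

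Table 2 then lists methods by outcome. Skin protection behaviour, action control and health-related quality of life get a linear mixed model. Self-assessed skin condition gets a generalised linear mixed model. Employment status and sick days each get "Descriptive; two-sample *t*-test".

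Sample size {14} allows for "an expected dropout rate of 30" per cent and notes that losses may turn out higher. Section {18b} says the questionnaires are posted with return envelopes. Section {18a} says sociodemographic data, including employment status, and the outcomes are collected at baseline.

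**The concern.** A two-sample t-test needs one observed value per person. Anyone without it drops out of the comparison, and nothing else known about that person enters. A mixed model keeps people with baseline or partial data and relies on missingness being at random given what was observed. The protocol makes a general inclusion statement and then, for two outcomes, names a method that cannot deliver it without a further step.

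Both outcomes are self-reported, and both are named in Objectives {7}. Someone who has left work or had long absences may be less likely to post a form back. Participants know their arm, and the control arm is waiting for app access, so return could also differ between arms. If it does, the comparison among returners may not reflect the comparison among all those allocated.

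**Working it through.** **1. Reproduce the plan's sample size.** Inputs from {14}: d = 0.4, two-sided alpha 0.05, power 0.80, equal arms, 30% dropout. The noncentral-t calculation gives 99.08 per arm, rounded up to 100, so 200 in total. Inflating for dropout: 200 / (1 − 0.30) = 285.7, rounded up to 286. This matches the stated N, so the plan itself expects about 200 people with 6-month data.

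**2. Number in each t-test.** Assume that the 30% also applies to the work outcomes:
- Analysed: 286 × 0.70 = 200.2, about 200 (about 100 per arm).
- Left out: 286 × 0.30 = 85.8, about 86.
- At assumed non-return of 20%, 40% and 50%, about 57, 114 and 143 are left out.

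**3. Set this beside the text.** Sections {20a} and {20c} include all randomised participants. Table 2 names a test that would include about 70% of them. Section {20c}, where a bridging step would be expected, offers only the mixed model, and ties its missing-at-random claim to the primary analysis.

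**4. When the between-arm difference is biased.** Let d be the non-return proportion in an arm, and k the difference, in SD units, between the mean of non-returners and the mean of returners in that arm. The returners' mean is then the full-arm mean minus d × k. The bias in the difference is −(d₁k₁ − d₀k₀). The values below are assumed; none comes from the document.

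| Non-return, arm 1 / arm 0 | k₁ / k₀ | Bias, absolute (SD) |
|---|---|---|
| 30% / 30% | 0.5 / 0.5 | 0 |
| 30% / 30% | 0.5 / 0.25 | 0.15 − 0.075 = 0.075 |
| 40% / 20% | 0.5 / 0.5 | 0.20 − 0.10 = 0.10 |
| 40% / 20% | 0.5 / 0 | 0.20 − 0 = 0.20 |

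Bias arises when non-return, or its link to outcome, differs between arms. It cancels when both are the same. The document gives no SD or event rate for either outcome, so neither the actual bias nor outcome-specific power can be computed.

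**The case against.** **The intention-to-treat sentence is mainly about assigned group and adherence.** It is contrasted with the per-protocol analysis, and a t-test by assigned arm fits that meaning. This is a fair reading of the emphasis. But the sentence also says that all randomised participants will be analysed, and {20c} repeats this under the heading that covers missing data. On that part the mismatch stands.

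**The document never says complete-case, and an unseen analysis plan could impute first.** This is true and would remove the conflict. The point is not that detail is absent. The article commits to a specific method that conflicts with its own inclusion statement, so the published wording would still need to agree with any such plan.

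**Stronger readings that the document does not support:**
- A reader might infer that the protocol claims missing-at-random validity for the work outcomes and then fails to deliver it. It claims this only for the primary analysis. The completer t-test rests on a more restrictive assumption than missing at random, not a weaker one.
- A reader might infer that any link between non-return and outcome within an arm biases the comparison. Step 4 shows that equal distortion in both arms cancels in the difference.
- A reader might build an example of false job-loss differences. Suppose true job loss is 20% in both arms, and forms are returned by 75% of those in work and by 50% (control) or 60% (intervention) of those who lost work. Returners then show 0.10/0.70 = 14.3% against 0.12/0.72 = 16.7%. All these rates are invented. With 50% in both arms the gap disappears. Because return depends on the unobserved outcome itself, a missing-at-random method would remove the gap only as far as observed data predict job loss.
- A reader might assume that work data exist at several follow-up points. Table 1 is not shown, so this cannot be confirmed.

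Section {12} already promises cautious interpretation of self-reported work outcomes. That is sensible, but it does not resolve the mismatch.

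**Conclusion.** The concern holds as an inconsistency between the stated inclusion rule and the method named for two secondary outcomes. At the plan's own dropout rate, each t-test would rest on about 200 of 286 participants and would ignore baseline employment and other data the trial holds. This assumes that the work outcomes are lost at the planned rate and that no unseen step precedes the test. Bias in the group difference is a risk, not a demonstrated effect, and its size cannot be derived from the document.

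The point is minor. The primary outcome, action control and quality of life use linear mixed models, and self-assessed skin condition uses a generalised one. None of these is affected.

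**What to change.** Preferred: replace the two t-tests in Table 2 with models suited to the data, binary or categorical for employment status and count for sick days, using baseline employment and other collected covariates.
- If these outcomes are reported at more than one follow-up, fit them as mixed models on all reports.
- If not, use multiple imputation by arm. Predictors should include earlier measurements already collected, such as the self-assessed skin grade, which the Limitations section places at all four time points.
- Keep the completer comparison as a sensitivity analysis, and say that missing-at-random methods help only as far as observed data predict the outcome.

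Minimum: if the t-tests stay, label them completer analyses, report the numbers analysed per arm, and limit the all-randomised-participants statement in {20a} and {20c} to the mixed-model outcomes.

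Cost: the minimum version is a few sentences. The preferred version needs some analysis time and a model or imputation specification fixed before the 6-month (t4) data are analysed. Neither needs new data. Recruitment is expected to run until October 2026, so there is time.
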